**WP1a: retrospective cohort study 1**		
	Incident cared for by YAS. Person aged ≥16 years (no upper age limit). (Those ≥16 account for 90% of incidents.^62^ Incident occurred between 1 February 2019 and 31 January 2020.* ‘Chief complaint’ (or other complaint) selected by attending ambulance clinician on PCR was ‘convulsions/fitting/seizure’ OR, if empty, call handler coded it as AMPDS protocol 12 (‘Convulsions’). No restriction on type of ambulance response incident received (ie, could have been ‘Hear & Treat’, ‘See & Treat’, ‘See & Convey to ED’ or ‘See & Convey elsewhere’†).	The <1% of events coded as AMPDSC02. These relate to seizures in someone potentially pregnant. (Guidelines state these should be conveyed because of eclampsia risk.^47^
**WP1b: Knowledge Exchange (KE) workshops**		
Service users	Aged ≥18 years (no upper age limit). Attended to by an ambulance during prior 12 months for a suspected seizure/s OR a significant other to such a person (eg, family member, friend). Incident could be related to epilepsy, non-epileptic attack disorder or syncope. (They account for ~70% of events.^127^ Able to provide informed consent and participate in a workshop independently in English. Lives in England.	Severe current psychiatric disorders (eg, acute psychosis). Terminal medical condition.
Clinicians	Aged ≥18 years (no upper limit). Ambulance clinician, ED doctor or nurse. Works in England. Able to provide informed consent and participate in a workshop independently in English.	Severe current psychiatric disorders (eg, acute psychosis). Terminal medical condition.
**WP2: retrospective cohort study 2**		
	Incident cared for by YAS. Person aged ≥16 years (no upper age limit). Incident occurred between 1 July 2021 and 30 June 2022.‡ ‘Chief complaint’ (or other complaint) selected by attending ambulance clinician on PCR was ‘convulsions/fitting/seizure’ OR, if field was empty, call handler coded it as AMPDS 12. No restriction on type of ambulance response incident received.	The <1% of events coded as AMPDSC02. These relate to seizures in someone potentially pregnant.
**WP3: ‘Next Steps’ workshops**		
	Aged ≥18 years (no upper limit). Ambulance clinician, seizure/epilepsy guideline developer, user group representative, seizure specialist (eg, neurologist/epilepsy nurse), commissioning representative. Able to provide informed consent and participate in a workshop independently in English. Lives in UK.	Severe current psychiatric disorders (eg, acute psychosis). Terminal medical condition.

*The time period does not include periods of industrial action; is before changes in use of acute services due to COVID-19 became apparent^128^; and is before the first UK COVID-19 fatality.^129^

†These are the labels used by the National Health Service (NHS) to record the main types of responses that ambulance services provide to incidents. Further detail is available from NHS England.^130^

‡This time period represents the most contemporary 12 months for which linked data will be available. It excludes COVID-19 national ‘lockdowns’ and the start aligns with when most COVID-19 legal restrictions in England were removed.

AMPDS, Advanced Medical Priority Dispatch System; ED, emergency department; PCR, patient care record; WP, work package; YAS, Yorkshire Ambulance Service.

The unit of analysis will be the patient, with the first recorded episode being the index event and subsequent episodes ≤3 days defined as recontacts (or 30 days for the secondary analysis).

##### Data extract

The data extract provided will include any ambulance, ED (Emergency Care Data Set; Hospital Episode Statistics (HES) Accident and Emergency (due to overlap in system use)), urgent inpatient (HES Admitted Patient) and death (ONS) records that relate to the index events which started within 30 days.

##### Outcome measures

Death/recontact with the UEC system following ambulance care and the likelihood of an AA occurring if conveyed to ED are important outcomes to clinicians and service users.^65^ Below we describe how the index events will be classified according to these two measures.

###### Measure 1 (safe/unsafe: death or recontact with UEC)

All index events, both conveyed and non-conveyed to ED, will be classified according to whether linked data indicate the patient involved died and/or recontacted the UEC (defined as any ambulance, ED or unscheduled inpatient care).

For the primary analysis, we propose a time frame of up to 3 days from the event within which death must have occurred or recontact started. This has been specified by paramedics and other stakeholders.^66^ It aligns with evidence that when considering *all* ambulance presentations, ~75% of deaths/UEC recontacts following non-conveyance occur within 3 days.^22^ We shall though still confirm its suitability with clinicians and service users via WP1b. For secondary analyses, a time frame of 30 days is proposed.^37 66–69^

Deaths within the cohort should be rare. Nonetheless, when describing and using deaths we shall report them with and without exclusion of persons where death was associated with end-of-life care.

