### Why is reducing clinically unnecessary conveyance important?

Clinically unnecessary conveyances to EDs result in ‘avoidable attendances’ (AAs).^9^ An AA is where the patient does not require the facilities of a type 1 ED to manage their healthcare problem. AAs can harm the patient^10^ and have implications for others since they restrict ED capacity.^11 12^ Approximately 15% of ED attendances currently meet O’Keeffe *et al*’s^9^ definition of an AA. In 2021/2022, this equated to ~2.3 million visits.^13^

Patients and the public are broadly supportive of non-conveyance. Research has identified that they are frustrated by inappropriate conveyance to ED and say assessment by an ambulance clinician itself has a therapeutic value.^14–21^

Importantly, UK data indicate non-conveyance following assessment by ambulance clinicians is safe. Overall, 83% of people experience no subsequent health event within 3 days of non-conveyance (9% recontact the ambulance service, 12.6% attend ED, 6.3% are admitted and 0.3% die).^22^

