### Current project

#### Overview and aims

To address the identified needs and information gaps, the 24-month mixed-methods RADOSS project is being completed. It has the following aims: (1) calculate the risks and benefits of conveyance to hospital after a suspected seizure; (2) create a risk prediction tool that predicts the likelihood that an individual will die and/or recontact the UEC system within 3 (and 30) days if not conveyed and the likelihood that their conveyance to ED would result in an AA; and (3) establish a pathway to clinical implementation of the risk prediction tool and maximise usage of RADOSS findings. The project’s related objectives were noted in table 1.

**Table 1 T1:** The RADOSS project’s aims and objectives and the work packages that address them

Aims	Objectives
(1) Calculate the risks and benefits of conveyance to hospital after a suspected seizure.	a. Describe the characteristics of those conveyed and those not conveyed to ED by one representative English ambulance service (WP1a).
	b. Compare the proportions following conveyance and non-conveyance that die and/or recontact the UEC within 3 (and 30) days (WP1a).
	c. Quantify the proportion of incidents conveyed to ED that meet the definition of an AA (WP1a).
(2) Create a risk prediction tool that predicts the likelihood that an individual will die and/or recontact the UEC system within 3 (and 30) days if not conveyed and the likelihood that their conveyance to ED would result in an AA.	d. Optimise the prediction tool development by completing KE workshops with service users and ambulance and ED clinicians to get views on predictors considered for inclusion in the models, the way the outcome measures of death, UEC recontact and AA are defined and risk score presentation (WP1b).
	e. Develop statistical models to predict a person’s risk of death/recontact with the UEC system within 3 (and 30) days and the likelihood of their attendance at ED being classed an AA if conveyed (WP1a).
	f. ‘Temporally’ validate the predictive models using data from the same ambulance service for a later time period (WP2).
(3) Establish a pathway to clinical implementation of the risk prediction tool and maximise usage of RADOSS findings.	g. Complete ‘next steps’ workshops with stakeholders to finalise plans to refine the tool for clinical use and its evaluation (WP3).
	h. Complete a proactive dissemination and knowledge mobilisation strategy (WP3, WP4).

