##### Sample size

Predictive models for the (1) risk of death/UEC recontact following conveyance, (2) risk of death/UEC recontact following non-conveyance, and (3) risk of an AA following conveyance could be developed. To permit robust testing of at least 40 candidate predictor parameters for each of these models, Riley *et al*’s^72^ formulae using standard parameters indicate: for model (1), a need for 2567 index events, with 103 experiencing the target event; for model (2), a need for 2194 index events, with 308 experiencing the target event; and for model (3), up to 2194 index events, with 461 experiencing the target event. Twelve months of YAS data should be sufficient to satisfy these requirements. Online supplemental file 3 details the reasons why and provides further information on the sample size calculation.

10.1136/bmjopen-2022-069156.supp3Supplementary data

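### Measure 1 counts a first ED attendance or admission as an event only for patients who were not conveyed, so the conveyed versus non-conveyed comparison partly reflects the event definition

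*Protocol article*

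**What the plan says.** The Measure 1 section applies one rule, labelled safe/unsafe, to both groups: "All index events, both conveyed and non-conveyed to ED, will be classified" by whether the patient "died and/or recontacted the UEC (defined as any ambulance, ED or unscheduled inpatient care"). The primary window is "up to 3 days from the event within which death must have occurred or recontact started"; 30 days is secondary.

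The unit-of-analysis statement after Table 4 (WP1a, Identification) fixes what a recontact is: the unit is the patient, "with the first recorded episode being the index event and subsequent episodes ≤3 days defined as recontacts".

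The two groups are then set against each other. Objective b in Table 1, under the aim on risks and benefits of conveyance, is "Compare the proportions following conveyance and non-conveyance that die and/or recontact the UEC within 3 (and 30) days". The WP1a Purpose section repeats this. The section on combining the models puts three outputs in one draft tool: the death/recontact risk under non-conveyance, the risk of the same name under conveyance, and the likelihood of an avoidable attendance (AA).

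The article does not say in so many words how the index ED visit, or an admission directly from it, is treated. It gives no alignment of the two groups, such as an outcome that does not depend on when hospital was reached.

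**The concern.** The rule is the same for both groups, but the index episode that it leaves out is not. For a conveyed patient, the index episode takes in the first ED attendance. For a non-conveyed patient, it ends on scene, so the first ED attendance or admission in the window is a recontact. Two patients with the same course (one ED visit, sent home, no further contact) can be classed as safe if taken at the first call and unsafe if they attended some hours later.

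Within a group this does no harm: it describes what follows that management. It matters where the two proportions are compared, or where the two predicted risks are shown under one name in a tool meant to inform conveyance. Part of the gap then comes from the definition, and the shift makes non-conveyance look worse, in a project that aims to reduce avoidable conveyance.

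**Working it through.** **1. What scores, by group (3-day window).**

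| Course | Conveyed at first call | Not conveyed at first call |
|---|---|---|
| One ED visit, sent home, nothing more | no event | event |
| One ED visit, admitted from it, nothing more | no event (inferred) | event |
| Later ambulance contact | event | event |
| Discharged from ED, then returns | event | event (already scored at the first visit) |
| Death | event | event |

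The asymmetry is confined to the first hospital contact.

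**2. Is the index ED visit really excluded?** The Sample size section gives the planned rates: "for model (1), a need for 2567 index events, with 103 experiencing the target event", and 308 of 2194 for the non-conveyed model.
- Conveyed: 103/2567 = 4.0%. Non-conveyed: 308/2194 = 14.0%. AA model: 461/2194 = 21.0%.
- These rates reproduce the stated sizes under the Riley criteria with P = 40 parameters. Shrinkage S = 0.9, optimism 0.05 and Cox-Snell R² = 0.15 are assumed, since the article says only that standard parameters were used.
- Criterion 1: n = P/((S − 1) ln(1 − R²/S)) = 40/(−0.1 × ln(1 − 0.15/0.9)) = 2194, which governs at 14% and 21%.
- Criterion 2 at 4%: maximum R² = 0.285; S = 0.15/(0.15 + 0.05 × 0.285) = 0.913; the same formula gives 2567, which governs.
- If the index ED visit counted, every patient conveyed to ED would have an event (100%). A planned 4% is possible only if it does not. For an admission directly from that visit, the exclusion rests on the words for recontact and subsequent episodes.

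**3. How much of the non-conveyed rate could be first hospital contact?** The only breakdown in the article is in the Introduction. It covers all presentations, 3 days after non-conveyance: 83% have no event, and "9% recontact the ambulance service, 12.6% attend ED, 6.3% are admitted and 0.3% die".
- Any event: 100 − 83 = 17%.
- Ambulance recontact or death, at most: 9 + 0.3 = 9.3 points. Hospital contact only, at least: 17 − 9.3 = 7.7 points; 7.7/17 = 45%.
- Any ED attendance: 12.6 points; 12.6/17 = 74%.

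**4. Applied to the planned 14% (assumption: seizures have the same mix).**
- Remove 45%: 14 × (1 − 0.453) = 7.7% remain; gap to 4% = 3.7 points.
- Remove 74%: 14 × (1 − 0.741) = 3.6% remain; gap = −0.4 points.
- Gap as planned: 14 − 4 = 10 points.

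The second case removes too much. At most 17 − 12.6 = 4.4 points lie outside ED attendance, so at least 9 − 4.4 = 4.6 points of ambulance recontact are removed with it, and these score in both groups. Nor is the first case a strict bound, since some hospital-only patients attend twice and a second visit would score in either group. The conveyed 4% was left untouched, although it may contain re-attendances.

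**5. The mechanism alone.** Suppose both groups have a 4% risk of every other kind of event, independent of a first ED contact. A first-contact risk of 5% to 12.6% (assumed range) puts the non-conveyed at 1 − 0.96 × 0.95 = 8.8% to 1 − 0.96 × 0.874 = 16.1%, against 4.0% conveyed, with no difference in anything else.

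**The case against.** The best defence is that Measure 1 asks a coherent question, namely what happens after the chosen management, and that index hospital care is examined elsewhere. Measure 2 classifies the index attendance as avoidable or not, the descriptive analysis tabulates discharge diagnoses and the reasons for not meeting the AA definition, and the tool shows the AA likelihood beside the two recontact risks. Deaths are reported separately from recontacts, and recontacts with and without AA-type contacts. Outcome definitions and risk presentation also go to the workshops.

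Much of this stands for each group on its own, but it does not repair the comparison. Dropping AA-type contacts leaves every first attendance with qualifying investigation or treatment, and every first admission, scoring only for the non-conveyed. If later attendances met the AA definition at the planned 21% (assumption), about 79% would remain. The workshop topics in Table 5 cover AA coding and the time frame, not this asymmetry.

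Three stronger readings are tempting and unsupported.
- A reader might set 17 − 12.6 = 4.4% beside the planned 4.0% and infer that the whole gap is an artefact. The two are not like for like, for the reasons in step 4.
- A reader might infer that counting index admissions would reverse the direction. The article gives no index admission share, so this cannot be said.
- A reader might infer that the comparison is bound to be read as non-conveyance being several times less safe. The Introduction itself reads a 17% event rate after non-conveyance as safe, so this is a risk of misreading and no more.

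**Conclusion.** The point holds as a fault in the comparison, not in the models. Objective b and the paired tool outputs compare two proportions that share a name but differ in what can count as an event, and the difference works against non-conveyance. The exclusion of index care is inferred: firmly for the ED visit, from wording alone for an admission directly from it.

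The size cannot be fixed from the article. Under the same-mix assumption, the planned 10-point gap would fall to about 3.7 points in one case and vanish in the other. Neither figure should be taken as an estimate: the mix is for all presentations, and the basis of the 14% and 4% is in a supplementary file not shown. The change is worth making before the comparison is run.

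**What to change.** Keep Measure 1 as the within-group outcome and as the outcome for each prediction model.

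For objective b, add a comparison on components defined identically from the event in both groups, at 3 and 30 days:
- death;
- death or any unscheduled admission, with admission from the index ED visit included.

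Report ambulance recontact after the index event separately. Report ED attendance descriptively in each group without comparing it, since every patient conveyed to ED has one. State that the groups differ by selection for conveyance, so that none of these contrasts is causal; this applies to index admission too. State in the Measure 1 section how the index ED visit and an admission directly from it are handled.

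In the draft tool, label the two death/recontact outputs as different outcomes whose difference should not be read as a difference in safety.

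Cost: re-tabulation from ambulance, ED, inpatient and death records that the planned extract already covers, plus wording. The downside is a short table in place of one headline proportion per group.

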### Routine data source: cured+

For WP1a and WP2, we will use a cutting-edge database called ‘CUREd+’. Currently being developed by the Centre for Urgent and Emergency Care Research,^64^ it will map UEC use by individuals served by the Yorkshire Ambulance Service (YAS) from 2011 to 2022. It contains records of all ambulance contacts and these are linkable to any subsequent ambulance, hospital (ED, inpatient) and death records (Office for National Statistics (ONS) mortality register). Further information is provided in table 3.

**Table 3 T3:** Key information about CUREd+ linked database

Issue	Detail
Linkage	CUREd+ is a prelinked data set. Events have been linked by NHS Digital using their algorithm based on NHS number, date of birth, postcode and sex.
Coverage of data	CUREd+ is new. Evidence from its predecessor CUREd (which mapped activity in the same area from 2011 to 2017 using a different approach^122^) indicates CUREd+ should have high data coverage. Evidence from CUREd and other work shows ~85% of individuals can have their ambulance and onward care records linked and so are suitable for inclusion.^104 123 124^ Wider work also shows those who can and cannot have their records linked do not markedly differ.^22^ CUREd+ could have even higher coverage due to more use of NHS numbers by ambulance services^125^ (which supports linkage).
Quality of data	The data contributing to CUREd were high in quality.^121 125 126^ Smyth^76^ examined ambulance patient care records (PCRs) for >22 000 patients. Most core clinical variables had <2% missing data and errors were rare. CUREd+ could have even higher quality due to the introduction of electronic PCRs (which support more consistent data capture).
Area covered by CUREd+ and suitability for RADOSS	England has 10 regional ambulance services. CUREd+ includes data from the Yorkshire Ambulance Service (YAS). The size of the population (~5.6 million) and geographical area (urban/rural mix, ~6000 square miles) served by YAS is similar to the average, as is its non-conveyance rate.^33^

NHS, National Health Service; RADOSS, Risk of Adverse Outcomes after a Suspected Seizure.

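### Measure 1 restricts inpatient recontact to unscheduled care but leaves ambulance and ED contact unrestricted, so planned ED reviews, and arguably inter-hospital transfers, can score as unsafe

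*Protocol article*

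**What the plan says.** The Measure 1 section of the protocol article labels each index event safe or unsafe. It applies to everyone: "All index events, both conveyed and non-conveyed to ED, will be classified". An event is unsafe if the patient died or "recontacted the UEC (defined as any ambulance, ED or unscheduled inpatient care". The primary window is a "time frame of up to 3 days from the event within which death must have occurred or recontact started"; the secondary window is 30 days.

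The Data extract section has the same pattern. It opens with "The data extract provided will include any ambulance, ED" and goes on to inpatient records, which alone are qualified as urgent. On the source database, the CUREd+ section says: "It contains records of all ambulance contacts and these are linkable to any subsequent ambulance, hospital (ED, inpatient) and death records".

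The outcome feeds three things: the comparison of conveyed and non-conveyed patients (Table 1, objective b), prediction models (1) and (2), and the draft tool that shows both risks to a clinician. WP2 uses the same outcome measures.

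**The concern.** Restricting inpatient care to unscheduled admissions shows that planned care is not meant to count as a bad outcome. The restriction is not carried to the other two limbs. Three examples, all within 3 days of the index event, show the effect of the literal rule:

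- Conveyed, discharged, and asked to return to the ED next day for a planned review: **unsafe**.
- Conveyed, admitted, and moved by ambulance to another hospital on day 2: **arguably unsafe**, depending on how recontact is read.
- Conveyed, discharged, and admitted electively on day 2: **safe**.

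If the first two kinds of contact are common enough, part of what models (1) and (2) predict is how hospitals arrange follow-up and transfers, not deterioration after the ambulance decision. The proportions reported under objective b would carry the same noise. The 30-day outcome leaves more time for planned reviews than the 3-day one.

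**Working it through.** **1. Does any other part of the article close the gap?**

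- *Identification* (text after Table 4) treats subsequent episodes inside the window as recontacts, without separating planned from unplanned.
- *Routine data source* states no exclusion of transfers: "It contains records of all ambulance contacts".
- *Describing sample and patient outcomes* gives recontact proportions with and without contacts that meet the avoidable-attendance definition. That drops a planned ED review only if it involved no qualifying investigation or treatment and ended in discharge. It is descriptive, is not stated to apply to the models, and does not address transfers.
- *WP1b* invites views on how recontact is defined, but the outcome row of Table 5 names avoidable-attendance coding and the time frame, not planned contacts.
- *Measure 2* foresees routine practice contaminating its own outcome and offers a conditional sensitivity analysis. For Measure 1, the only with/without rule in its own section concerns end-of-life deaths.

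No passage excludes planned ED returns or transfers from the modelled outcome.

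**2. Planning rates, from the Sample size section**

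The article states "for model (1), a need for 2567 index events, with 103 experiencing the target event", and 308 events in 2194 for model (2).

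- Model (1), conveyed: 103/2567 = 4.01%.
- Model (2), non-conveyed: 308/2194 = 14.04%.

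As a check that these are the design rates, take the Riley criteria with P = 40 parameters. The article refers only to standard parameters, so shrinkage S = 0.90, Cox-Snell R² = 0.15 and an optimism limit of 0.05 are assumed.

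- Shrinkage criterion: n = P / [(S − 1) ln(1 − R²/S)] = 40 / [(−0.1) ln(1 − 0.15/0.9)] = 2194.
- Optimism criterion: the same formula with S = R² / (R² + 0.05 × max R²). At a 4% rate max R² = 0.2853, so S = 0.15/0.16427 = 0.9132 and n = 2567. At 14% it gives 1309.
- The larger value is 2567 for model (1), with 2567 × 0.04 = 102.7 events, and 2194 for model (2), with 2194 × 0.14 = 307.2 events. Both stated sizes are reproduced.

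The sample size calculation is not in error.

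**3. Weight of the same misclassification in each model**

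Let q be the percentage points that planned contacts add to a genuine rate p. Their share of scored events is q/(p + q). The documents give no q, so the values below are assumed.

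| q (points) | Model (1), p = 4% | Model (2), p = 14% |
|---|---|---|
| 0.5 | 0.5/4.5 = 11% | 0.5/14.5 = 3% |
| 1 | 1/5 = 20% | 1/15 = 7% |
| 2 | 2/6 = 33% | 2/16 = 13% |

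For the same q, the share in model (1) is about three times that in model (2).

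**4. Effect on the planned contrast**

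In the most unfavourable of these cases, 2 points are added to conveyed patients and none to non-conveyed patients. The contrast then moves from 4% against 14% to 6% against 14%. The direction holds.

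**5. If the 4% already includes such contacts**

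The genuine rate would be 3.5%, 3% or 2% for q = 0.5, 1 or 2, which is about 90, 77 or 51 of the 103 events (2567 × 0.035, 0.03, 0.02).

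**The case against.** The strongest reply is that the parenthesis defines urgent and emergency care in a condensed article. Inpatient data contain a large elective stream and so need the word unscheduled, whereas ED and emergency ambulance care are urgent by nature. On that reading the text is not contradictory, and code-level rules may sit in a full protocol or analysis plan that is not shown. This is a fair account of how the wording arose. It does not change what the wording does: a stated outcome rule admits planned contacts on two limbs and bars them on the third.

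On transfers, one can say that a patient moved by the hospital has not recontacted anything, and that the article does not say transfers are among the ambulance records. That stands, and this example is only arguable. The planned ED review is the firmer one.

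A reader might infer that these contacts fall mainly on conveyed patients, inflate their rate and tilt objective b towards non-conveyance. Patients just seen in hospital are the likelier recipients of hospital-arranged contacts, so this is plausible. The documents give neither a frequency nor a split, so they do not support it as a finding. Nor can the reported rate be said to rise above 4%: the basis for that figure is in a supplement not shown, and it may already count such contacts.

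An any-contact outcome is also simple and defensible, and filtering on routine codes brings errors of its own. Both points favour keeping it as a sensitivity analysis.

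**Conclusion.** The point holds in a limited form and is a cheap improvement. The definition treats planned inpatient care one way and planned ED or ambulance contact another, and nothing in the article corrects this for models (1) and (2). Some planned contacts would therefore be scored unsafe. How many is unknown.

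What can be said about size is relative: for equal absolute misclassification, model (1) is about three times as exposed as model (2), because it plans on 4.0% rather than 14.0%. The shares of 11%, 20% and 33% rest on assumed additions of 0.5, 1 and 2 points to a genuine 4% and are not estimates. The direction of the planned contrast survives even when the largest of these is added to one group alone.

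**What to change.** Define recontact as *any unscheduled ambulance, ED or inpatient contact*. Where the fields are in the extract, do not count ED attendances coded as planned follow-up or ambulance journeys coded as inter-facility transfers. Use the same rule in WP2, so that derivation and validation share one outcome. Tabulate the removed contacts by conveyance group, for 3 and 30 days; this also supplies the missing frequency. Keep the unrestricted definition as a sensitivity analysis for the proportions and for models (1) and (2).

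The cost is one wording change and a code filter, reliance on routine codes whose availability and quality are not described, and probably slightly fewer target events. If the 4% already includes planned contacts, the model (1) requirement under the assumptions in the check would rise from 2567 to 2801, 3105 or 4126 at genuine rates of 3.5%, 3% or 2%. The achieved number of conveyed events should be compared with this once the tabulation is available. If planned contacts prove rare, the tabulation will show it and little is lost.

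### The 3-day recontact clock starts at the event for conveyed patients too, so part of any lower recontact after conveyance may be time spent in hospital

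*Protocol article*

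**What the plan says.** Measure 1 (WP1a, Outcome measures) covers both groups: "All index events, both conveyed and non-conveyed to ED, will be classified according to whether linked data indicate the patient involved died" or recontacted urgent and emergency care (UEC). Recontact is "defined as any ambulance, ED or unscheduled inpatient care". The primary window is fixed by "we propose a time frame of up to 3 days from the event within which death must have occurred or recontact started", and on the longer window the protocol adds: "For secondary analyses, a time frame of 30 days is proposed". The text after Table 4 uses the same origin, "with the first recorded episode being the index event and subsequent episodes ≤3 days defined as recontacts", with 30 days for the secondary analysis.

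Table 1, objective b, compares the resulting proportions directly between conveyed and non-conveyed patients. The section on combining the models puts the conveyed risk (model 1) and the non-conveyed risk (model 2) into one draft tool.

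Measure 2 recognises that some conveyed patients are admitted, and Measure 1 expects deaths to be rare. The planned variants concern recontacts that are themselves avoidable attendances, patients who refused conveyance, and end-of-life deaths. None starts a clock at discharge, separates admitted patients or deals with inpatient time. The data extract holds "records that relate to the index events which started within 30 days".

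**The concern.** Recontact means a new ambulance, ED or unscheduled inpatient contact. A patient left at home can generate one throughout the 72 hours. A conveyed patient can do so only after leaving the ED or ward, and one who stays 3 days or more cannot do so at all within the primary window. Since deaths should be rare, recontact drives the composite.

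Two results are exposed. In objective b, lower recontact after conveyance would mix any true benefit with lost opportunity to recontact. In model (1), predictors of admission also predict lost opportunity, so they may look protective.

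The planned safeguards do not address this. The figure supporting 3 days (about 75% of deaths and recontacts) is for patients who were not conveyed. The Knowledge Exchange workshops ask which time frame is most useful, not where the clock starts for conveyed patients. WP2 uses the same outcome measures, so temporal validation would carry the same feature forward. Models (2) and (3) are not affected.

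**Working it through.** **1. The plan's own figures.** The WP1a Sample size section gives 2567 index events with 103 target events for model (1), and 2194 with 308 for model (2). The implied planning risks are 103/2567 = 4.0% and 308/2194 = 14.0%. The totals reproduce exactly from the cited sample-size formulae with 40 parameters, a Cox-Snell R² of 0.15 and risks of 0.04 and 0.14. The R² and the rounded risks are inferred; the article does not state them.
- Shrinkage criterion: 40/[(0.9 − 1) × ln(1 − 0.15/0.9)] = 2194. This governs model (2), and 0.14 × 2194 gives 308 events after rounding up.
- Optimism criterion at a risk of 0.04: maximum R² = 0.285, so S = 0.15/(0.15 + 0.05 × 0.285) = 0.913, and 40/[(S − 1) × ln(1 − 0.15/S)] = 2567. This governs model (1), and 0.04 × 2567 gives 103 events.

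The sample sizes are not in dispute. They serve here only to give the planning risks.

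**2. Share of the conveyed 3-day window at risk.** Let f be the share of conveyed patients admitted and g the share of those staying 3 days or more. Take the remaining stays as uniform on 0.5 to 3 days (mean 1.75). All of this is assumed.

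Share at risk = (1 − f) + f(1 − g)(1 − 1.75/3)
- f = g = 0.3: 0.70 + 0.30 × 0.70 × 0.417 = 0.787
- f = g = 0.5: 0.50 + 0.50 × 0.50 × 0.417 = 0.604

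**3. What an event-based 4% would then mean.** With a constant hazard, the equal-exposure risk is 1 − (1 − 0.04)^(1/share).
- Share 0.787: 5.05%
- Share 0.604: 6.53%

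**4. A wider grid.** Suppose 20 to 50% are admitted, with a common stay of 1 day up to 3 days or more. Blocked share = admitted share × min(stay, 3)/3.
- Lowest: 0.2 × 1/3 = 7%. Highest: 0.5 × 3/3 = 50%.
- With a true risk of 14% in both groups, conveyed patients would show 14% × 0.933 = 13.1% down to 14% × 0.5 = 7.0%.
- Taking the stated minimum numbers (2567 and 2194) as group sizes, equal true risks of 14% and 10%, 20% or 30% of opportunity blocked, the probability of a nominally significant difference (two-sided 5%) is about 0.30, 0.83 or 0.99. The expected direction favours conveyance.

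**5. Could it explain the planned gap?** The blocked share needed is 1 − 4.01/14.04 = 71%, above every value in the grid.

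**6. At 30 days.** Blocked share = admitted share × stay/30. With stays of 1 to 5 days it runs from 0.2 × 1/30 = 0.7% to 0.5 × 5/30 = 8%.

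**7. Direction of predictors in model (1), illustration only.** Suppose a marker raises true risk from 4% to 6%, and 60% of its carriers but 10% of other patients are inpatients for the whole window. The observed risks are 6% × 0.4 = 2.4% and 4% × 0.9 = 3.6%, so the marker looks protective.

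**The case against.** The strongest reply is that the origin is right for the purpose. The tool supports an on-scene decision; death or recontact within 3 days of that decision is a coherent quantity with the same start in both groups, and time in hospital is a consequence of conveying. This stands. Unequal time at risk is a defect only if the result is read as comparative safety outside hospital. Objective b and the side-by-side display in the tool invite that reading, so the feature needs to be shown rather than removed.

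A reader might infer that a discharge-based outcome should become primary. The documents do not support that. It would mix two origins: for a patient admitted for 10 days, recontact would be counted on days 10 to 13 while a death on day 8 would fall outside the 3-day limit. Patients who die in hospital would never become at risk of recontact.

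A reader might also take the recontact definition to count the index ED visit itself. The text after Table 4 limits recontacts to subsequent episodes, and a 4% planning risk for conveyed patients would be impossible if every index ED visit counted. What remains is that no sentence says how an admission directly following the index attendance is treated; counting it would push the bias the other way.

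Finally, the 4% is a planning input whose basis lies in a supplementary file not shown, so it need not be an event-based observed rate. The protocol also describes most suspected seizures as low risk, and the assumed admission rates and stays have no support in it.

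**Conclusion.** The point holds in a limited form. The primary 3-day recontact outcome gives admitted conveyed patients less opportunity to recontact, and nothing planned separates that from safety in objective b or model (1). On the narrower assumptions an event-based 4% corresponds to about 5.1 to 6.5%; on the wider grid, 7 to 50% of the conveyed opportunity is blocked. These figures rest on assumed admission shares, assumed lengths of stay and a constant recontact hazard.

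The documents do not establish that conveyance will look safer than it is by any particular amount, that the artefact accounts for the planned 4% v 14% difference, that the 30-day results are materially affected, or that any predictor's sign will in fact reverse. In-hospital deaths within the window are still counted. The point calls for an added analysis and a clearer definition, not replacement of the primary outcome.

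**What to change.** - Keep the event-based definition as the result tied to the on-scene decision.
- State that the index ED attendance and any directly following admission belong to the index episode and are not recontacts.
- For objective b and model (1), add a 3-day analysis with recontact counted from discharge from the index episode and death still counted from the event. Report how many conveyed patients die before discharge, since they never become at risk of recontact.
- Report conveyed patients discharged directly from ED separately from those admitted.
- Label model (1) in the draft tool so that users see its risk runs from the event and includes time in hospital.

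The cost is a little extra analysis. Discharge dates should already be in the ED and inpatient records requested. The calendar windows will differ between groups in the added analysis, which is why it sits beside the event-based result. Since the extract covers records starting within 30 days, 3 days from discharge is observable for stays of up to about 27 days; it needs extending only if 30 days from discharge is also wanted.
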